## Abstract

**Background:**

Autism spectrum disorder (ASD) is a complex neurodevelopmental disorder characterized by impairments in social interaction and communication. Oxytocin (OXT), as a neuropeptide, plays a role in emotional and social behaviors. *Lactobacillus reuteri* (*L. reuteri*) supplementation led to an OXT-dependent behavioral improvement in ASD mouse models. Despite some promising results from animal studies, little is known about the efficacy of supplementation with *L. reuteri*, alone or with exogenous OXT therapy, on social-behavioral functions in ASD patients. This paper presents a protocol for a pilot randomized controlled trial to evaluate the feasibility of conducting a full trial comparing oral supplementation of *L. reuteri* probiotics and intranasal OXT spray to placebo on the effect of social and behavioral functions in ASD patients. The study will also capture preliminary estimates of the efficacy of the proposed interventions in ASD patients.

**Methods:**

This pilot trial is a two-staged, randomized, double-blind, placebo-controlled, parallel-group study. Throughout the study (0–24 weeks), 60 patients with ASD will be randomly assigned to receive either oral *L. reuteri* probiotics or placebo. In the second study stage (13–24 weeks), all participants will receive intranasal OXT spray. As primary outcomes, serum OXT levels will be assayed and social behaviors will be assessed via the Autism Behavior Checklist and the Social Responsiveness Scale which are validated questionnaires, an objective emotional facial matching test, and a new video-based eye-tracking test. Secondary outcomes include the GI-severity-index and Bristol Stool Chart to assess GI function and gut microbiome/short-chain fatty acids. All the outcomes will be assessed at baseline and weeks 12 and 24.

**Discussion:**

This pilot study will provide important information on the feasibility of recruitment, blinding and concealment, treatment administration, tolerability and adherence, specimen collection, outcome assessment, potential adverse effects, and the preliminary efficacy on both primary and secondary outcomes. If successful, this pilot study will inform a larger randomized controlled trial fully powered to examine the efficacies of oral *L. reuteri* probiotics and/or intranasal OXT spray on social-behavioral improvement in ASD patients.

**Trial registration:**

ClinicalTrials.gov, NCT03337035. Registered 8 November 2017.

## Background

Autism spectrum disorder (ASD) is a complex neurological and developmental disorder characterized by impaired communication and social interaction skills, as well as stereotypical repetitive behavioral patterns. In the United States of America (USA), the prevalence of ASD has nearly tripled from 1 in 150 as of 2000 to 1 in 59 as of 2018 [1]. Its etiology remains elusive, but some pathophysiological findings may shed light on its effective treatment [2–4].

Oxytocin (OXT) is a hypothalamic neuropeptide of multiple functions, including modulation of emotional and social communication, bonding, and reward-related behaviors [5]. In murine studies, mice with a deficiency of OXT signaling (OXT ligand or receptor knockout and genetically deficient oxytocin exocytosis models) all displayed autistic-like behavior [6, 7]. There is also some evidence from humans showing OXT deficiency in ASD subjects [8]. Thus, dysfunction of OXT signaling has been implicated to play an important role in the etiology of ASD [9, 10]. As an easily administered and cost-effective treatment with possibly minimal adverse effects, OXT holds promising therapeutic potential in treating ASD core symptoms [1]. Andari et al. reported that in a small randomized placebo-controlled trial wherein 13 patients with high functioning autism had improved social recognition and attention to social cues after OXT administration [11]. A meta-analysis of 12 randomized controlled trials (RCT) of OXT on social recognition of ASD patients showed no evidence of significant efficacy of OXT compared with placebo [12]; however, the level of such overall evidence was low due to substantial between-trial heterogeneity, including variations in study design, patient characteristics, primary outcome assessments, and OXT dosage and duration. In addition, ASD patients may vary in the functionality of their endogenous OXT system, and it is possible that only the subgroups that are more genetically prone to OXT signaling dysfunction may respond well to OXT treatments.

Of note, OXT signaling may be a key link in the gut-brain axis and seems inducible by certain probiotics. Poutahidis et al. [13] first described the induction of endogenous OXT signaling by *Lactobacillus reuteri* probiotics in animal studies; subsequent animal studies provided consistent evidence of OXT-dependent behavioral improvement in multiple ASD mouse models after supplementation with the *L. reuteri* [14–16]. Previous studies showed that *L. reuteri* probiotics reduced responses to negative emotional stimuli in amygdala, insula, and fronto-limbic regions, compared with placebo [17, 18].

Based on the promising results of previous studies, we proposed our central hypothesis that supplementation with *L. reuteri* probiotics, independently or in combination with intranasal OXT treatment, would lead to improvement of social and behavioral functions in ASD patients via induction of OXT signaling. So far, none of the published studies has reported the efficacy of *L. reuteri* in ASD patients. Further, there are no trials that specifically examine the synergistic effects between *L. reuteri* and OXT therapy. We thus designed a pilot randomized clinical trial to evaluate the feasibility of recruitment, blinding and concealment, treatment administration, tolerability and adherence, specimen collection, outcome assessment, and potential adverse effects as well as preliminary results on primary and secondary outcomes. This pilot study will inform future design of a fully powered trial, which would provide direct evidence on the potential efficacy of *L. reuteri* single therapy and *L. reuteri plus* OXT dual therapy for targeting the ASD core symptoms.

## Methods

### Study design

This protocol describes a pilot trial to test the study feasibility and intervention tolerability and is available online at ClinicalTrials.gov (NCT03337035). The study will be reported in accordance with the Template for Intervention Description and Replication and the Consolidated Standards of Reporting Trials.

We designed a two-staged, randomized, double-blinded, placebo-controlled, parallel-group clinical trial. Figure 1 outlines the study flowchart and Table 1 timetable for data collection. In the first stage of this pilot trial, we will randomly assign 60 patients, with a 1:1 ratio, to either *L. reuteri* treatment or placebo in order to assess the effects of 12-week administration of *L. reuteri* alone on the behavioral measurements of ASD, and whether treatment response depends on the degree of baseline OXT level and/or endogenous OXT signaling induction by *L. reuteri* probiotics. At least 30 participants are needed in each arm to test the acceptability and tolerability of intranasal OXT spray with either *L. reuteri* or placebo treatment. In the second stage of the trial, we will add intranasal OXT to both groups while their *L. reuteri* or placebo treatment continues for an additional 12 weeks to explore the possibility of synergy between exogenous intranasal OXT and endogenous OXT induction by *L. reuteri*. We anticipate that the 12-week treatment duration will be sufficient for *L. reuteri* supplementation to induce detectable changes in OXT, gut microbiome, and social awareness/behavioral scores.

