### Study procedure

The treatment will proceed for a total of 24 weeks (Fig. 1 and Table 1). In the first stage (12 weeks), all the patients will be randomly assigned to two groups: group A (30 subjects) receives oral *L. reuteri* probiotics while group B (30 subjects) receives oral as a placebo. We decided on a 12-week timeline because according to the most recent systematic review of probiotics therapy in ASD, the average duration of clinical trials is 3 months [19]. In the second stage, subjects in group A and group B will continue their respective oral *L. reuteri* probiotics or placebo administration as in stage 1. In addition, both groups will be simultaneously administered with intranasal OXT spray for an additional 12 weeks. We will stratify patients according to their ASD severity based on screening questionnaires and diagnostic evaluations.

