### Sample size and power calculation

This project is intended to evaluate the feasibility of implementing an oral supplementation of *L. reuteri* probiotics with and without an intranasal OXT spray therapy to inform an eventual larger-scale randomized trial that will allow for a more rigorous assessment of the efficacies of the proposed single or dual interventions. Hence, our sample size is calculated based solely on the primary outcomes: (1) scores of behavioral assessment questionnaires, including the ABC and SRS-2; (2) scores of objective ASD behavioral tests, including eye-tracking and emotional face matching tests; and (3) serum OXT changes. To achieve statistical power of 80% with an overall one-sided significance level of alpha = 0.10, if we assume a large effect size of 0.8 (Cohen’s *d*) in each of primary outcomes for the effect of *L. reuteri* probiotics alone vs *L. reuteri* probiotics plus OXT therapy, an estimated number of 26 ASD patients in each group would be needed based on independent two-sample *t* test. If a potential noncompliance or dropout rate of 10% is assumed, we plan to enroll 60 autistic subjects totally for this pilot study. Sample size calculation was carried out using the PASS 16 Power Analysis and Sample Size Software (NCSS, LLC. Kaysville, Utah).

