### Feasibility target

Feasibility targets will be set to greater than or equal to 30 enrollments per 6 months, greater than or equal to 70% adherence rate, and greater than or equal to 70% data collection completion rate.

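### The stated minimum of 30 per arm for testing the oxytocin spray has no allowance for losses before the spray starts at week 13 (minor)

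*Protocol article*

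**What the plan says.** The protocol article gives two minimum sizes per arm, in different sections and for different purposes.

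- **Tolerability of the spray (Study design).** "At least 30 participants are needed in each arm to test the acceptability and tolerability of intranasal OXT spray with either" the probiotic or placebo. Shortly before this, the same section says "we will randomly assign 60 patients, with a 1:1 ratio", and Study procedure repeats the group size: "group A (30 subjects) receives oral" probiotic, with 30 in group B.
- **Primary outcomes (Sample size and power calculation).** This section bases its calculation on the primary outcomes alone and arrives at 26 per group. It then adds: "If a potential noncompliance or dropout rate of 10% is assumed, we plan to enroll 60 autistic subjects totally for this pilot study".
- **Start of the spray (Abstract, Methods).** "In the second study stage (13–24 weeks), all participants will receive intranasal OXT spray". The first 12 weeks are probiotic or placebo only.

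**The concern.** A minimum number needed to test a treatment has to be met by people who receive that treatment. Here the minimum equals the number randomised, and 12 weeks pass before anyone gets the spray. The plan itself expects some loss, but its allowance was built on the 26 and not on the 30. The two sizes therefore do not fit together: one carries a margin for loss and the other carries none.

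Tolerability is not a side issue in this pilot. Study design names it as something the trial is meant to test, and the Discussion says the focus is on acceptability and tolerability of the dual therapy. If the report later shows 28 or 29 per arm starting the spray, the trial will have missed its own stated minimum, although nothing went worse than planned.

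**Working it through.** **Inputs.** Randomised per arm: 30 (Study design, Study procedure). Stated need for testing the spray: at least 30 per arm (Study design). Need for the primary outcomes: 26 per group (Sample size and power calculation). Noncompliance or dropout: 10% (same section). Spray starts at week 13 of 24 (Abstract, Methods).

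**Step 1: reproduce the plan's enrolment.** Needed per arm = 26 / (1 − 0.10) = 28.9, rounded up to 29; 2 × 29 = 58. The planned 60 covers this. In the other direction, 30 × 0.90 = 27, which is above 26. The primary-outcome size survives a loss of up to 4 of 30, or 13.3%. This part of the plan is consistent. (How the 26 itself was obtained is a separate question and does not affect this point.)

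**Step 2: apply the same allowance to the 30.** Treat the whole 10% as dropout. This is an assumption, since the plan combines dropout with noncompliance and a noncompliant participant may still start the spray. The number starting the spray then depends on timing:

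| Timing of the 10% loss (assumed) | Expected to start the spray, per arm |
|---|---|
| All after week 12 | 30 |
| Half in weeks 0–12 | 30 × 0.95 = 28.5 |
| All in weeks 0–12 | 30 × 0.90 = 27 |

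Only the first row meets the stated minimum.

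**Step 3: chance that an arm keeps all 30 to week 13.** With independent losses this is (1 − loss)^30. At 5% stage-1 loss: 0.95^30 = 0.21. At 10%: 0.90^30 = 0.04.

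**Step 4: what the shortfall costs in precision.** If none of n participants has a given event, the one-sided upper 95% bound on its rate is 1 − 0.05^(1/n).

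- n = 30: 1 − 0.05^(1/30) = 9.5%
- n = 27: 1 − 0.05^(1/27) = 10.5%

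The worst case under the plan's own loss rate costs one percentage point.

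**Step 5: what it would take to keep the 30 as a minimum.** If all of the 10% fell in stage 1, 30 / 0.90 = 33.3, so 34 per arm and 68 in total. Step 4 shows that this would buy very little.

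**The case against.** **The 30 may mean allocated participants.** The sentence comes soon after the 1:1 allocation of 60 and speaks of each arm. On that reading 30 randomised satisfies it, and the text does not mention completers. This reading is possible but weak: the sentence ties the 30 to testing the spray, and someone who leaves before week 13 never receives it and contributes nothing on its tolerability.

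**Losses after week 13 should not count.** This stands. A participant who starts the spray and stops is tolerability information, not a loss to that assessment. The relevant number is therefore those who start, 27 to 30 per arm, and not the roughly 27 who would complete.

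**The effect is small.** This also stands, and it sets the severity.

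**A stronger reading that a reader might infer.** The Feasibility target section accepts "greater than or equal to 70% data collection completion rate". Taken as participants, 70% of 30 is 21 per arm, below both 30 and 26, so it is tempting to say that the plan does not deliver its 26 either, or that the target must be raised to 52/60 = 87%. The document does not support this. The 70% is a minimum criterion for calling the pilot feasible, not the expected retention; its unit (participants, visits or items) is not defined; and the planning assumption is 10%, under which 27 remain. A feasibility threshold looser than the planning loss rate is not a contradiction. Nor does it imply inadequate power on the stated terms: with 21 per arm, an effect size of 0.8 and the stated one-sided 0.10, a two-sample t test has 90% power, above the planned 80%. Lower figures need a significance level that the document does not state, or an assumed dilution of the effect by nonadherence.

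**Conclusion.** The point holds for one sentence, at minor severity. The minimum of 30 per arm for testing the spray is not secured by the plan's own figures, because the number randomised equals the minimum, the spray starts after 12 weeks, and the 10% allowance was never applied to it. About 27 to 30 per arm can be expected to start the spray, and 28 to 29 if losses are spread evenly. These numbers assume that all of the 10% is dropout; the even spread is a further assumption, because the timing is not stated. The worst case in that range raises the zero-event upper bound from 9.5% to 10.5%. The enrolment of 60 and the 26 per group are sound relative to each other, and nothing here calls for a larger trial or a different feasibility target.

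**What to change.** Keep the total at 60. In Study design, replace the statement that at least 30 per arm are needed with text along these lines: *Thirty participants will be randomised to each arm. Allowing for up to 10% dropout, about 27 to 30 per arm are expected to start intranasal oxytocin at week 13. Tolerability will be summarised among all who start it, including those who stop early. If no event of a given kind is seen in an arm, the one-sided upper 95% bound on its rate would be 9.5% with 30 participants and 10.5% with 27.*

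The cost is a change of wording in one place. Sample size, randomisation, feasibility targets and the primary-outcome calculation stay as they are. The stated tolerability size becomes slightly less favourable, but it is one the plan can meet under its own loss assumption.

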**Fig. 1 Fig1:**
[figure not shown]
Study design. OXT oxytocin, ABC Aberrant Behavior Checklist, SRS social responsiveness scale, GSI gastrointestinal severity index, Gaba gamma-aminobutyric acid, IL interleukin, TGF tumor growth factor, IFN interferon, GFAP glial fibrillary acidic protein, MBP myelin basic protein, TNF tumor necrosis factor, fMRI functional magnetic resonance imaging, *L. reuteri Lactobacillus reuteri*

**Table 1 Tab1:** Study schedule of enrollment, interventions, and assessments

	Study period				
	Screening	Baseline	Follow-up		Post-trial
Visit		1	2	3	
Time point		Day 0	Week 12	Week 24	Week 36
Enrollment					
Eligibility screening	X				
Written informed consent		X			
Randomization and allocation (after eligibility criteria met and written informed consent obtained)		X			
Interventions					
First stage: *L. reuteri* vs placebo			X		
Second stage: *L. reteri* plus OXT spray vs placebo plus OXT spray				X	
Assessments					
Past medical history and medications	X				
Surveys (ABC, SRS-2, GSI, and microbiome)		X	X	X	
Labs (OXT and fecal microbiome)		X	X	X	
Tests (emotion matching and eye-tracking)		X	X	X	
Adverse events			X	X	X

*OXT* oxytocin, *ABC* Aberrant Behavior Checklist, *SRS* social responsiveness scale, *GSI* gastrointestinal severity index, *GABA* gamma-aminobutyric acid, *IL* interleukin, *TGF* tumor growth factor, *IFN* interferon, *GFAP* glial fibrillary acidic protein, *MBP* myelin basic protein, *TNF* tumor necrosis factor, *fMRI* functional magnetic resonance imaging, *L. reuteri Lactobacillus reuteri*

### Ethical considerations

The current protocol has received the Institutional review board (IRB) approval at Massachusetts General Hospital (IRB protocol number: 2017P001667), and any potential amendments will be submitted for evaluation in a timely manner. All studies will be performed with the approval of Partners Human Research Committee. Informed consent for the study will be obtained in-person at the initial study visit, after inclusion criteria have been met and prior to any experimental procedure. This will be conducted in a private room by a physician-investigator. The investigator will explain the purpose, procedures, and potential discomforts and risks of the study before obtaining signed informed consent and assent from one parent and, if applicable, from the prospective subject. Subjects 7–13 years old will sign a separate assent form, and subjects 14–15 years old will give assent on the consent form. Subjects will receive copies of the consent and assent forms.

### Participants

All the participants should meet the inclusion criteria as follows:
Age between 3–25 years old;Preexisting diagnosis of autism and confirmation of diagnosis by both the Diagnostic and Statistical Manual of Mental Disorders (DSM)-V-TR criteria, as well as the Autism Diagnostic Observation Schedule (ADOS) and/or Autism Diagnostic Interview-Revised (ADI-R);Physical capacity to go to a clinic for visits;Stable medications for at least 4 weeks (whatever medications that patients were taking at the start of the trial);No planned changes in medications or psychosocial interventions during the trial; andWillingness to provide blood samples.

Participants with any of the following conditions will be excluded:
Pregnant or breast-feeding woman (before or during the study);Comorbidity of other neurological and/or psychiatric disorders, including unstable seizure, schizophrenia, schizoaffective disorder, bipolar disorders, or history of substance abuse;History of oxytocin, antibiotics, or probiotic use in the month prior to enrollment;Subjects with active cardiovascular disease that is not controlled by medication;Regular nasal obstruction or nosebleeds;Significant hearing or vision impairments; andHabitual consumption of large volumes of water.

ASD diagnostic criteria: Diagnostic and Statistical Manual of Mental Disorders (DSM)-V-TR is published by the American Psychiatric Association and offers a common language and standard criteria for the classification of mental disorders. It is used, or relied upon, by clinicians, researchers, psychiatric drug regulation agencies, health insurance companies, pharmaceutical companies, the legal system, and policy makers together with alternatives, such as the ICD-10 Classification of Mental and Behavioral Disorders, produced by the WHO. The ADOS is a semi-structured assessment of communication, social interaction, and play (or imaginative use of materials) for individuals suspected of having autism or other pervasive developmental disorders. The ADI-R is a structured interview conducted with the parents of individuals who have been referred for the evaluation of possible autism or autism spectrum disorders.

### Recruitment and screening procedures

ASD patients will be recruited from primary care, pediatric, and ASD clinics at Massachusetts General Hospital (MGH), Beth Israel Deaconess Medical Center, community ASD education events, and charity ASD programs in Boston as well as participants from overseas. Screening will be performed by trained staff members via phone calls at A. Martinos Center for Biomedical Imaging, MGH. Informed consent will be obtained in-person at the initial study visit, and minors will require assent and consent of at least one parent or legal guardian.

### Description of randomization and blinding

Randomization and allocation concealment will be performed in collaboration with Massachusetts General Hospital (MGH) research pharmacy. Randomization sampling numbers will be electronically generated, and central randomization at the research pharmacy using coded drug containers of identical appearance prepared by the research pharmacy will ensure allocation concealment. Blinding will be maintained by making the capsules look identical. Both participants and the research staff who collect the outcome data will be blinded to treatment status.

### Study procedure

The treatment will proceed for a total of 24 weeks (Fig. 1 and Table 1). In the first stage (12 weeks), all the patients will be randomly assigned to two groups: group A (30 subjects) receives oral *L. reuteri* probiotics while group B (30 subjects) receives oral as a placebo. We decided on a 12-week timeline because according to the most recent systematic review of probiotics therapy in ASD, the average duration of clinical trials is 3 months [19]. In the second stage, subjects in group A and group B will continue their respective oral *L. reuteri* probiotics or placebo administration as in stage 1. In addition, both groups will be simultaneously administered with intranasal OXT spray for an additional 12 weeks. We will stratify patients according to their ASD severity based on screening questionnaires and diagnostic evaluations.

